## Abstract

**Background:**

Depression and chronic musculoskeletal pain (CMSP) are the leading causes of years lived with disabling diseases worldwide. Moreover, they often commonly coexist, which makes diagnosis and treatment difficult. A safe and effective treatment is urgently needed. Previous studies have shown that acupuncture is a cost-effective treatment for simple depression or CMSP. However, there is limited evidence that acupuncture is effective for depression comorbid with CMSP.

**Methods:**

This is a randomized, sham acupuncture-controlled trial with three arms: real acupuncture (RA), sham acupuncture (SA), and healthy control (HC). Forty-eight depression combined CMSP participants and 12 healthy people will be recruited from GDTCM hospital and randomized 2:2:1 to the RA, SA, and HC groups. The patients will receive RA or SA intervention for 8 weeks, and HC will not receive any intervention. Upon completion of the intervention, there will be a 4-week follow-up. The primary outcome measures will be the severity of depression and pain, which will be assessed by the Hamilton Depression Rating Scale (HAMD-17) and Brief Pain Inventory (BPI), respectively. The secondary outcome measures will be cognitive function and quality of life, which will be measured by the Montreal Cognitive Assessment (MoCA), P300, and World Health Organization Quality of Life (WHOQOL-BREF). In addition, the correlation between brain-derived neurotrophic factor (BDNF) and symptoms will also be determined.

**Discussion:**

The aim of this study is to evaluate the clinical efficacy and underlying mechanism of acupuncture in depression comorbid with CMSP. This study could provide evidence for a convenient and cost-effective means of future prevention and treatment of combined depression and CMSP.

**Trial registration:**

Chinese Clinical Trial Registry ChiCTR1800014754. Preregistered on 2 February 2018. The study is currently recruiting.

## Background

Chronic musculoskeletal pain (CMSP) and depression are the leading causes of years lived with disabling disease worldwide [1]. Moreover, CMSP and depression are highly intertwined and could exacerbate one another’s symptoms [2, 3]. Unfortunately, the overlapping symptoms lead to poor physical functional outcomes, longer duration of symptoms, and lower treatment response. This places a profound burden on both individuals and society. Notably, this burden far exceeds social service capacity.

The high prevalence of depression and CMSP comorbidity may indicate a common pathogenesis. Both depression and chronic pain are associated with cognitive function [4]. An increasing number of studies have shown that people who suffer from chronic pain or depression have poor performance on cognitive function tests [5, 6]. Other studies found that cognitive function acts as a protective factor against the emergence of chronic pain. Brain-derived neurotrophic factor (BDNF) is a member of the neurotrophin family, which is crucial for the survival and neuroplasticity of neurons. Decreased BDNF levels and increased BDNF methylation status, especially in the promoter regions of exons I and IV, were identified in patients with depression [7, 8]. More interestingly, after antidepressive treatment, BDNF methylation decreased, and serum BDNF levels increased [9, 10]. Some studies have demonstrated that serum BDNF levels are tightly correlated with the course of depression [11]. Thus, some scientists consider BDNF and BDNF promoter methylation to be biomarkers for depression [10, 12–14].

Acupuncture has been widely used to improve chronic pain and depression [15–17]. However, research on depression comorbid with chronic pain is rare. A randomized, controlled trial of acupuncture or counseling compared with usual care for depression showed that acupuncture is a cost-effective treatment for depression patients with or without comorbid pain [18]. However, the evidence on the effect of acupuncture is not conclusive. Therefore, we propose to conduct a pilot RCT of acupuncture on comorbid mild-moderate depression and CMSP. The objective of this study is to (1) determine the clinical efficacy of acupuncture on comorbid mild-moderate depression and CMSP and (2) investigate the association between BDNF and comorbidity of depression and CMSP.

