### Types of participants

In this trial, we will recruit mild-moderate depression comorbid CMSP patients and healthy participants. Healthy participants need to meet the following criteria: no history of depressive disorder, a score on the 17-item Hamilton Depression Rating Scale (HAMD-17) < 8; no chronic pain in the past 3 months; and no complications of severe systemic diseases such as diabetes mellitus, tumors, or other conditions considered unsuitable to participate in the trial. CMSP patients with mild-moderate depression need to meet the following criteria.

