### Inclusion criteria

Participants will be included if they meet the following criteria:
Meet the criteria of DSM-5™ and ICD-10 for mild-moderate depression;HAMD-17 ≤ 24 and ≥ 8;Suffering chronic musculoskeletal pain (location at the neck, back, and limb) more than 3 months and VAS score ≥ 4;Aged between 18 and 65;No acupuncture therapy during the past 3 months before enrollment; andVoluntarily participating in this trial with a written informed consent form.

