#### Secondary outcomes

Secondary outcomes include the rates of depression response and remission at the 8th week (endpoint), where response is defined as a reduction of 50% of the HAMD-17 score and remission as a HAMD-17 score of 7 or less [22]; the rates of pain response at the 8th week, where response is defined as a reduction of 2 points of the BPI-WP [23, 24]; the Beijing version of Montreal Cognitive Assessment (MoCA); the World Health Organization Quality of Life BREF (WHOQOL-BREF); event-related potential (P300); and the serum level of BDNF and DNA methylation of BDNF. The Beijing version of the MoCA is highly recommended as a clinical and research tool for evaluating cognitive impairment. Previous studies proved that B-MoCA has a reliability of 0.73 Cronbach’s alpha in patients with obstructive sleep apnea-hypopnea syndrome with cognitive impairment [25]. The total MoCA score is 30 points, and less than 26 points is considered to indicate cognitive impairment. In addition, P300 will be used as an objective index to measure cognitive impairment, because it is based on the electrophysiological brain response. Previous studies have shown a decrease in amplitude and an increase in latency in depression patients [26]. The WHOQOL-BREF is an abbreviated version of the WHOQOL-100, which contains 26 items. In this trial, the official Chinese version of the WHOQOL-BREF, which has been approved by the WHOQOL Group [27], will be used to evaluate the changes in quality of life. BDNF is a biomarker for depression patients [14, 28]. All depression and CMSP participants will receive blood tests and P300 tests at baseline and 8 weeks. ELISA, RT-PCR, and BSP will be applied to measure the serum BDNA level and BDNF DNA methylation. The correlation between BDNF and symptoms will be determined.

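### Objective 2 is worded as linking BDNF to the comorbidity of depression and CMSP, but the design compares only people with both conditions and people with neither, so it should be narrowed to severity within the patients and analysed with depression and pain in one model

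*Protocol article*

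**What the plan says.** The protocol article states two objectives at the end of its Background. The second is to "investigate the association between BDNF and comorbidity of depression and CMSP".

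Under Types of participants, "we will recruit mild-moderate depression comorbid CMSP patients and healthy participants". The Inclusion criteria require both conditions of every patient: "Meet the criteria of DSM-5™ and ICD-10 for mild-moderate depression" and "Suffering chronic musculoskeletal pain (location at the neck, back, and limb) more than 3 months and VAS score ≥ 4". Healthy controls must have neither: "no history of depressive disorder, a score on the 17-item Hamilton Depression Rating Scale (HAMD-17) < 8" and "no chronic pain in the past 3 months". Study design lists three groups only (real acupuncture, sham acupuncture, healthy control), and Sample size calculation sets them at 24, 24 and 12.

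Patients give blood at baseline and week 8 (Secondary outcomes); healthy controls give it at baseline only (Intervention). Two analyses of BDNF are named. Secondary outcomes says "The correlation between BDNF and symptoms will be determined", and the Abstract says the same in substance. Statistical analysis of the trial outcomes assigns paired t tests to the blood measures.

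The article also treats BDNF as a marker of depression in its own right. The Background reports lower BDNF and higher methylation in depressed patients, and Secondary outcomes states that "BDNF is a biomarker for depression patients".

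**The concern.** To associate a marker with comorbidity, as distinct from either component, some people must have one condition without the other. This trial enrols none. Among the patients, comorbidity does not vary. Between patients and healthy controls, depression and chronic pain change together.

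What is at stake is the interpretation of one of the two stated objectives. A lower BDNF level in patients than in controls could be reported as a finding about the comorbidity, although the article's own background makes depression alone a ready candidate explanation. A correlation of BDNF with pain scores could likewise be read as a pain finding when it only reflects that patients with more pain are also more depressed.

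**Working it through.** The article gives no figure for this objective, so there is none to reproduce. The check is whether the effects can be identified.

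**Step 1. Which cells are filled.** Let D = 1 for depression and P = 1 for CMSP.

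| | P = 1 | P = 0 |
|---|---|---|
| D = 1 | 48 patients | none |
| D = 0 | none | 12 healthy controls |

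**Step 2. What the groups can estimate.** Write mean BDNF = b0 + b1·D + b2·P + b3·D·P.

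- Patients: b0 + b1 + b2 + b3.
- Healthy controls: b0.
- Difference: b1 + b2 + b3.

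Only this sum is estimable. The design matrix has rank 2 for four parameters. Using patients alone the rank is 1; with all four cells filled it would be 4. The same observed difference δ follows from depression alone (b1 = δ), pain alone (b2 = δ), the combination alone (b3 = δ) or any mixture. More participants, better matching of controls or a different test leaves this unchanged.

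**Step 3. What the named analyses address.** Paired t tests describe within-person change from baseline to week 8. The BDNF-symptom correlation describes severity among people who all have both conditions. Neither is a contrast on comorbidity status.

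**Step 4. Why separate correlations are not enough.** Suppose BDNF depends on depression severity only. Then its simple correlation with pain is the product of the BDNF-HAMD-17 correlation and the HAMD-17-BPI correlation. The article gives neither, so both are assumptions here. Take 0.4 in size for the first and 0.3, 0.5 or 0.7 for the second. The apparent BDNF-pain correlation is then 0.4 × 0.3 = 0.12, 0.4 × 0.5 = 0.20 or 0.4 × 0.7 = 0.28, with no pain association given depression. A model containing both scales removes this component.

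**Step 5. Precision of the narrower question.** At two-sided 0.05 and 80% power, the detectable simple correlation is tanh[(1.96 + 0.84)/√(n − 3)]. This is 0.39 for n = 48 and 0.43 for n = 41 (48 × 0.85 = 40.8, using the article's 15% dropout). In the joint model each standard error grows by about 1/√(1 − r²), where r is the HAMD-17-BPI correlation: 1.05, 1.15 and 1.40 for r = 0.3, 0.5 and 0.7. Eligibility also restricts the ranges: HAMD-17 from 8 to 24, and pain VAS from 4 to below 7.

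**Step 6. The both-versus-neither contrast, if it is made.** For 48 versus 12 (58 degrees of freedom, two-sided 0.05), 80% power needs a standardized difference of about 0.92. Under assumed true differences of 0.5, 0.8 and 1.0, power is 33%, 68% and 86%. These figures are the same whichever of b1, b2 and b3 produces the difference.

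**The case against.** The strongest reply is that the article mostly uses comorbid as the name of the patient population. Read that way, objective 2 asks how BDNF relates to the illness these patients have, and the planned BDNF-symptom correlation answers it. No hypothesis, endpoint or test claims to separate comorbidity from single conditions. The study calls itself a pilot, BDNF is one of several secondary outcomes, and leaving out single-condition groups is a legitimate choice of scope.

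Much of this stands. The answerable question is already in the plan, so the defect is a mismatch between the objective's wording and what the design and analyses deliver. But the wording sets what the trial may conclude. The reply also does not cover separate correlations, which confound the two severities.

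Three stronger readings are tempting and are not supported:

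- **That depression alone fully explains any patient-healthy difference.** The article's statements about BDNF in depression show that it could. Aliasing means the sources cannot be separated; it does not show that pain contributes nothing.
- **That 33%, 68% and 86% are rates of false support for objective 2.** They are ordinary power for a patient-versus-healthy test that the statistical section does not name, at effect sizes the article does not give. They become misleading only if a real both-versus-neither difference is attributed to comorbidity.
- **That the mechanism statement in the Discussion falls as well.** It concerns how acupuncture works, a question for change over time and for real versus sham acupuncture. It does not need single-condition groups.

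**Conclusion.** The concern holds in a limited form. As worded, objective 2 refers to an association with comorbidity that this design cannot separate from depression alone or pain alone. This follows from the eligibility criteria and the three groups, and rests on no numerical assumption. The planned symptom correlation addresses a different and answerable question, and it would be better served by a joint model.

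This is a worthwhile, inexpensive improvement and not a threat to the trial. It affects the wording and interpretation of the second objective. It does not affect the real-versus-sham comparison, the primary outcomes or the sample size. The correlations in Step 4 and the effect sizes in Step 6 are assumptions for scale; the conclusion does not depend on them.

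**What to change.** 1. Restate objective 2 along these lines: to estimate the association of serum BDNF and BDNF methylation with depression severity (HAMD-17) and pain severity (BPI) in patients with comorbid depression and CMSP.
2. Analyse it with one model in the patients that includes HAMD-17 and BPI together, so that each association is estimated given the other. Report estimates with confidence intervals.
3. Report any baseline BDNF difference between patients and healthy controls as descriptive of both conditions versus neither, and state that it cannot be attributed to comorbidity.

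Cost: rewording and one regression on data already to be collected, with no new groups or patients. The claim becomes narrower, and the joint estimates will be imprecise with at most 48 patients and restricted severity ranges. Keeping the present wording as a question about comorbidity itself would require depression-only and CMSP-only groups, a much larger change that this point does not call for.

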## Methods

### Study design

This project is a randomized controlled clinical trial with 3 groups: real acupuncture (RA), sham acupuncture (SA), and healthy control (HC) at a ratio of 2:2:1. This trial was approved by the ethics committee of Guangdong Provincial Hospital of Chinese Medicine (Z2017-162-01). Before randomization, written informed consent will be obtained from all participants prior to their involvement. Primary and secondary outcome measures will be assessed at baseline, 4, 8, and 12 weeks. Outcome assessors and statisticians will be blinded in this study. An overview of the trial is shown in Fig. 1. This protocol was reported according to the Standard Protocol Items: Recommendation for Interventional Trials (SPIRIT) statement requirements. The complete SPIRIT checklist is available in Additional file 1 and Fig. 2.

**Fig. 1 Fig1:**
[figure not shown]
Flowchart of trial procedures

**Fig. 2 Fig2:**
[figure not shown]
SPIRIT figure

### Types of participants

In this trial, we will recruit mild-moderate depression comorbid CMSP patients and healthy participants. Healthy participants need to meet the following criteria: no history of depressive disorder, a score on the 17-item Hamilton Depression Rating Scale (HAMD-17) < 8; no chronic pain in the past 3 months; and no complications of severe systemic diseases such as diabetes mellitus, tumors, or other conditions considered unsuitable to participate in the trial. CMSP patients with mild-moderate depression need to meet the following criteria.

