### Exclusion criteria

Participants with the following conditions will be excluded:
Suicidal ideation or SCL-90 depression score > 26;Bipolar disorder or schizophrenia;Malignant pain caused by cancer pain syndrome;Suffering severe pain, VAS ≥7;Headache and visceral pain such as stomachache;Pregnant or breastfeeding women;Complications of severe systemic diseases such as diabetes mellitus, tumors, or others considered not suitable to participate in the trial; andHad acupuncture treatment in the last 3 months.

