### Recruitment of participants

This trial will take place at the outpatient department of acupuncture and moxibustion, Second Affiliated Hospital of Guangzhou University of Chinese Medicine, China. Outpatients will be recruited via posters in the hospital and via Internet advertisement.

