### Statistical analysis of the trial outcomes

Outcome data will be analyzed according to the intention-to-treat principle, including all randomly assigned participants after baseline assessment regardless of whether they receive the intervention. Missing data will be replaced by the data from the latest assessment. The outcome data will be analyzed with SPSS (version 22.0; SPSS Inc., Chicago, IL, USA). Descriptive statistics (variance analysis, non-parametric test, chi-square test) will be used to summarize demographic features among the three groups. The HAMD-17, BPI, MoCA, and WHOQOL-BREF will be analyzed using the repeated measures method, and post hoc comparisons will be evaluated with the Bonferroni test. The rates of depression/pain response and depression remission will be analyzed by the chi-square test. P300 and blood measures will be analyzed by paired *T* tests.

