## Discussion

Depression and CMSP commonly coexist, which makes clinical treatment very difficult [29]. Despite huge costs, current pharmacological and psychological interventions have limited acceptability and effectiveness. Thus, patients are keen to have a cost-effective treatment. According to the American College of Physicians, acupuncture increases the response to second-generation antidepressants [30]. Previous studies also showed that acupuncture has clinical efficacy on depression and related symptoms, such as insomnia [15, 17, 18]. A systematic review showed that acupuncture is a cost-effective treatment for chronic pain [31]. Whether acupuncture has clinical efficacy on combined depression and CMSP is uncertain. On this basis, we designed this study, which meets CONSORT guidelines [32]. This trial will provide evidence on the clinical efficacy of acupuncture as a potential treatment for comorbid depression and CMSP. In addition, we will explore the mechanism of acupuncture’s antidepressant and analgesic effects from an epigenetic perspective.

Even so, there are some limitations of this study. First, it is a single-blind study, which may cause partial bias in the results. We will try our best to overcome this bias by allocating the different groups in different places to receive treatment. Second, the adherence of participants may be poor because the treatment period lasts 8 weeks. The study size is calculated on the hypothesis of a 15% loss rate, but it will be necessary to ascertain that there is no bias between the two intervention groups. Third, in this study, we performed a 4-week follow-up, and long-term follow-up will be more credible. Finally, there will be a skewed sex ratio in this study, because in traditional Chinese culture, men are generally unwilling to seek help, especially for mental disease. This bias was also present in our previous study.

We have presented the design and protocol for the clinical efficacy of acupuncture on mild-moderate depression comorbid with CMSP. On completion, this study will validate the clinical efficacy of acupuncture and its underlying mechanism.

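### Healthy controls get no age range, fewer listed exclusions and no balancing on age or sex, so the baseline patient-versus-healthy contrast in BDNF and P300 is open to confounding

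*Protocol article*

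**What the plan says.** All places are in the Protocol article.

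- **HC criteria (Types of participants).** The list begins "Healthy participants need to meet the following criteria: no history of depressive disorder". It then requires HAMD-17 below 8 and freedom from chronic pain over the preceding 3 months. Its last item concerns general health: "no complications of severe systemic diseases such as diabetes mellitus, tumors, or other conditions considered unsuitable to participate in the trial". It names no age range, sex criterion or matching.
- **Patient criteria.** The same section ends with "CMSP patients with mild-moderate depression need to meet the following criteria", which assigns the two lists that follow to the patients. Inclusion criteria has "Aged between 18 and 65". Exclusion criteria has "Bipolar disorder or schizophrenia", and also excludes pregnancy or breastfeeding and acupuncture in the last 3 months.
- **Role of HC.** Randomization places healthy participants in the HC group directly, without randomising them. Intervention limits their tests to blood and P300 at baseline. The Background gives the association between BDNF and the comorbidity as the second objective.
- **Sex ratio (Discussion).** "there will be a skewed sex ratio in this study", explained by men's reluctance to seek help, above all for mental illness.
- **Analysis (Statistical analysis of the trial outcomes).** Variance analysis, non-parametric and chi-square tests "will be used to summarize demographic features among the three groups". P300 and blood measures are to be compared by paired t tests.

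**The concern.** HC are not randomised, so their comparability with the patients rests on how they are selected. Their only evident use is a baseline contrast with the patients on BDNF and P300: they have no other measurement after eligibility and no follow-up. If HC differ from the patients in age or sex, and the markers vary with age or sex, that contrast mixes disease with demography.

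The plan itself points to one route to imbalance. Reluctance to seek help can skew the sex ratio of patients who present for care, but it has much less bearing on healthy volunteers. Nothing in the plan works against the resulting difference. An analysis plan cannot repair this fully, because it cannot restore an age range that was not applied at enrolment, and 12 HC leave little room to adjust away a large imbalance.

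**Working it through.** **1. The two sets of criteria side by side**

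| Item | Patients | HC |
|---|---|---|
| Age | 18 to 65 | not stated |
| Bipolar disorder or schizophrenia | excluded | only through the unsuitable-condition clause |
| Pregnancy or breastfeeding | excluded | only through that clause |
| Acupuncture in last 3 months | excluded | only through that clause |
| Severe systemic disease | excluded | excluded |
| Sex or age balance with the other group | – | none |

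The patients' lists cannot be read as covering HC, since they require depression and chronic pain.

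**2. The plan's own figure**

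48 patients in two arms of 24 at 2:2:1 give 48/4 = 12 HC, as stated.

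**3. How large the confounding could be**

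From the documents: 48 patients, 12 HC, α = 0.05. Assumed, because the documents give no values: a two-sided test, equal variances, no true disease effect, an age–marker correlation of 0.3 to 0.5, an age shift of 0.5 or 1 SD, 70–85% women among patients against 50% among HC, and a sex effect of 0.3 to 0.5 SD.

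Formulas:
- Bias from age = (age shift in SD) × (correlation).
- Bias from sex = (difference in share of women) × (sex effect in SD).
- False-positive rate = rejection probability of the t test with 58 degrees of freedom and noncentrality bias / √(1/48 + 1/12) = bias / 0.323.

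| Scenario | Bias (SD) | False-positive rate |
|---|---|---|
| Age shift 0.5 SD | 0.5 × 0.3 = 0.15 to 0.5 × 0.5 = 0.25 | 7.4% to 11.9% |
| Age shift 1 SD | 0.30 to 0.50 | 15.0% to 33.2% |
| Sex alone | 0.20 × 0.3 = 0.06 to 0.35 × 0.5 = 0.175, rounded to 0.18 | 5.4% to 8.5% (8.3% at the unrounded 0.175) |

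**4. Would the three-group demographic test show the imbalance?**

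With groups of 24, 24 and 12 and only HC shifted by δ SD, the overall mean is 12δ/60 = 0.2δ. The noncentrality of the F test (2 and 57 degrees of freedom) is 48 × (0.2δ)² + 12 × (0.8δ)² = 9.6δ².

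- δ = 0.5: noncentrality 2.4, detected 25% of the time.
- δ = 1: noncentrality 9.6, detected 78% of the time.

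The test is therefore weak against the moderate shift, where the false-positive rate is 7–12%. It is fairly sensitive to the larger shift, where the rate is 15–33%.

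**The case against.** Several points on the other side have weight.

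- **The contrast is implied.** No patient-versus-HC test is named. It follows from the BDNF objective and from HC having blood and P300 tests at baseline only. It concerns secondary, mechanistic markers in a study that calls itself a pilot. This stands and limits the weight of the point.
- **Exclusions are partly covered.** The systemic-disease exclusion is shared, and the unsuitable-condition clause could catch psychosis or pregnancy. Other patient exclusions, such as severe or cancer pain, add little for pain-free people. This stands too, but a discretionary clause sets no age limit and cannot balance sex.
- **Adjustment may sit elsewhere.** Covariate adjustment and detailed matching rules may be in an analysis plan or full protocol that is not shown, so their absence is not the charge. The charge is that the article does state HC criteria, and that they differ from the patients'.

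A reader might also infer three stronger things that the documents do not support:

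- **That the contrast is confounded.** The actual imbalance is unknown and could be negligible. The Discussion expects a skewed ratio in the study as a whole and does not say that HC will differ from patients.
- **That recruitment source is a further confounder.** Recruitment of participants says "Outpatients will be recruited via posters in the hospital and via Internet advertisement", but the Abstract names the same hospital as the source of both patients and healthy people.
- **That the demographic test would usually miss any imbalance that matters.** It would flag a 1 SD age shift about 78% of the time. The 25% detection rate belongs with the 0.5 SD shift and its 7–12% rate, not with the 15–33% rate.

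**Conclusion.** The point holds in a limited form. As written, the plan lets HC fall outside the patients' age range, leaves three patient exclusions to discretion for HC, and balances neither age nor sex. The baseline contrast in BDNF and P300 is therefore open to confounding by age and sex.

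Under the assumed values the effect runs from small to material. Sex alone, at 5.4–8.5%, barely moves the error rate. A moderate age shift roughly doubles it at most, to 7–12%, and would often go unflagged. A large age shift raises it to 15–33% but would usually be flagged. All these rates rest on assumed shifts, correlations and sex effects, and none is an estimate for this trial.

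The randomised comparison of real with sham acupuncture, including both primary outcomes, is unaffected. This is a worthwhile improvement to a secondary aim and not a flaw in the main trial.

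**What to change.** - **Types of participants:** apply to HC the 18 to 65 age range and the applicable patient exclusions (bipolar disorder or schizophrenia, pregnancy or breastfeeding, recent acupuncture).
- **HC selection:** frequency-match the 12 HC to the enrolled patients on sex and age band, for example by filling four sex-by-age cells in proportion to the patients.
- **Analysis:** adjust the baseline patient-versus-HC contrast for age and sex whatever the demographic tests show, and report standardised patient–HC differences in age and sex beside the three-group p-values.

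The first two changes work only at enrolment. The article reports recruitment as open, so they can reach only HC not yet enrolled.

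The cost is protocol wording and slightly slower HC recruitment, since a few volunteers are turned away once a cell is full. HC numbers stay at 12, and no procedure is added.
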